## Abstract

**Background:**

Low-quality social relationships in older adults are strongly associated with feelings of loneliness. Physical activity interventions could reduce loneliness and improve psychological well-being, among other health benefits. The aim of this study is to examine the feasibility of a Physical Activity Intervention for Loneliness (PAIL) in community-dwelling older adults at risk for loneliness.

**Methods/design:**

This feasibility study is a two-arm randomised controlled trial (RCT) with a wait-list control group using a mixed-methods research design. The primary aim of the feasibility study is to estimate recruitment, retention and adherence rates; the appropriateness of the intervention design and its practicality; the acceptability of the intervention by participants; and the set of instruments and measures and primary outcome measures to inform a future large-scale randomised trial. After eligibility screening, randomisation will be conducted using computer-based random sequence generation. Baseline and post-intervention assessments for intervention and control groups will include height, weight, body mass index, resting blood pressure, physical activity using accelerometry, loneliness, social support, social networks, anxiety and depression, self-efficacy for exercise, satisfaction with social contacts, and expected outcomes and barriers for exercise using questionnaires. Focus groups will be conducted at the mid-point and post-intervention period using a phenomenological approach to analyse the participants’ experiences of taking part in PAIL.

**Discussion:**

This trial will provide important information regarding the feasibility of PAIL in community-dwelling older adults at risk for loneliness using a mixed-methods approach combining quantitative and qualitative research methods.

**Trial registration:**

Clinicaltrials.gov NCT03458793

**Electronic supplementary material:**

The online version of this article (10.1186/s40814-018-0379-0) contains supplementary material, which is available to authorized users.

## Background

Maintenance of social connectedness throughout the lifespan is an important aspect of successful ageing [1]. The disruption of established social patterns or poor quality of social relationships negatively impacts quality of life and well-being in older adults and is highly associated with loneliness [2, 3]. According to UK statistics, loneliness is highly prevalent and increasing among older adults aged 65 years or older [4]. Further, 11% of people aged 75 years and older reported to have no close friends and visited their general practitioner (GP) to fulfil their need to talk to somebody [4]. Defined as a discrepancy between a person’s desired and actual social relationships [5], loneliness and a lack of social relations were considered to be high-risk factors for morbidity and mortality, and the negative impact of loneliness can be as harmful as smoking 15 cigarettes a day [6, 7]. Bearing in mind the ageing of the UK population, with a sharp increase in the proportion of adults aged 65 years and older over the last 30 years [8], health professionals have placed special emphasis on the promotion of “active ageing” enabling older adults to increase participation in “social, economic, cultural, spiritual and civic affairs” to maintain quality of life [9]. Further, promotion of a variety of campaigns to prevent loneliness [10–12] may reduce or slow the burden on NHS expenses, with potential economic benefits estimated at around £900 per annum per person associated with loneliness reduction [10]. Given this, the early prevention of loneliness and timely implementation of health interventions in a community setting to tackle the problem at its early onset seems prudent.

Physical activity (PA) is defined as any bodily movement produced by the contraction of skeletal muscles that results in a substantial increase over resting energy expenditure [13, 14]. It is a health behaviour that can facilitate meaningful social relationships and serve as an alternative to medical treatments which may have negative side effects [11, 15, 16]. Compared to other forms of treatment therapies (e.g. mindfulness therapy, art and craft therapy), physical activity interventions, especially in small groups (up to eight to nine people), can assist in building friendly and trusted relationships between participants based on shared interests and similar needs, as demonstrated by previous research [12, 17].

Mechanisms of physical activity interventions’ effectiveness are suggested to relate to loneliness reduction models, stress reduction and increased social support during activities. Related to the first mechanism, the social compensation model [18] suggests that PA can work via compensation for lost meaningful social connections due to increased peripheral social networking during friendly conversations between participants [17]. The hypothesis of the broaden-and-build theory of positive emotions [19] posits that enjoyable forms of PA generate happiness and bring positive emotions, which in turn could be associated with loneliness reduction as shown in a longitudinal study Newall et al. [20]. The tripartite model of group identification was found to be effective, particularly among lonely seniors, based on the sense of identification and social attraction to group members with shared interests and goals, arising during engagement in physical activities [21]. Related to the second mechanism, based on the stress/social support model [22], social networks promote well-being that is associated with loneliness reduction in older adults. Among the mechanisms named above, only the tripartite model of group identification was shown to be successfully applied in the treatment of loneliness directly in the context of PA.

Based on the analysis of existing randomised controlled trials (RCTs), there are few PA interventions for loneliness reduction conducted with residents in community settings [23]. This is also in line with previous systematic reviews and meta-analyses [2, 15, 24–30]. A subsequent analysis for other loneliness-related social outcomes has shown that for social functioning (as a sub-domain of health-related quality of life), specific aspects of PA interventions can successfully influence social health [23] with the strongest effects being obtained for group setting exercise interventions, with delivery by a health/medical professional, in a diseased rather than healthy population. PA interventions did not appear to be effective for increasing social support or social networks [23]. In addition, the majority of studies used a cross-sectional design, which does not allow determination of causality and limits the rigour of the research evidence. However, longitudinal studies do not always support the direct effects of PA interventions on loneliness reduction in older adults [15]. Nevertheless, it is important to emphasise that the majority of existing PA interventions assess loneliness as a secondary outcome within a number of other psychosocial outcomes, which limits the ability to fully examine these interventions’ effectiveness for reducing loneliness [15, 31].

Further, a number of moderating (affecting the strength of the relationship between PA and loneliness) and mediating factors (driving the influence of PA on loneliness) are not consistently considered in intervention studies, making the outcomes of even well-conducted interventions less credible [15]. Research shows that global- [32, 33] and domain-specific self-efficacy [34] are moderating factors, and social support was found to be both a moderating [35] and mediating factor [36]. Also, perceived self-efficacy in one study by Fry and Debats [34] was found to be a superior predictor of loneliness and psychological distress in older adults compared to demographic factors, physical health and support networks. Further, personal (self-efficacy) and environmental (social support) variables moderating relationships between loneliness and PA have a bidirectional link with each other [37]. Perceived social support is a moderator of self-efficacy, and increased self-efficacy leads to better social support [35].

Bearing in mind the limitations of the current literature as presented above, understanding the mechanisms of association between loneliness and PA may bring new insights to the designing of novel and effective PA interventions [15]. Further research is needed to explore the association between loneliness, self-efficacy and social support in the context of PA interventions for older adults. However, before the mechanisms can be fully understood, the practicalities and feasibility of implementation of such interventions with older adults must be tested. The aim of the study is an examination of the feasibility of RCT of Physical Activity Intervention for Loneliness (PAIL) in community-dwelling older adults at risk for loneliness. For the planned future large-scale RCT, the primary hypothesis is that, compared with the inactive control group, participants in the intervention group will report a greater decrease in loneliness. The secondary hypothesis is that participants in the intervention group will significantly increase their amount of physical activity engagement per week, and this will be associated with greater positive changes in other psychosocial and health outcomes compared to control group participants.

### Study objectives

The following specific aims of this feasibility study are to estimate:Recruitment rate, attendance and retention rates (number of participants completing the study as a proportion of those randomised)The appropriateness and practicality of the designed intervention in the proposed settingsThe acceptability of the intervention by participants and willingness to participateThe appropriateness of the assessment toolsThe appropriateness of the statistical methods of data analysis usedThe power calculation of the likely required sample size for a future large-scale RCT.The acceptability of measures and the most suitable primary outcome measure for a future large-scale RCT

In addition, to reflect the aims of a future large-scale RCT that this feasibility study seeks to inform, the effect sizes between the intervention and control groups will be examined.

## Methods/design

PAIL is a tw0-arm RCT of a 12-week intervention compared with a wait-list control (WLC) condition using a mixed-methods research design (including quantitative and qualitative research methods). Quantitative data will be collected from the intervention and control groups at the baseline and immediate post-intervention periods. Qualitative data aimed to assess the appropriateness, practicality and acceptability of the designed intervention in the proposed settings will be collected at the mid-point and post-intervention period. The trial was approved by the Science, Technology, Engineering and Mathematics (STEM) Research Ethics Committee of the University of Birmingham, UK (ERN_16-1419A). Consent forms (Additional file 1) will be obtained from all participants prior to entry into the study. This protocol for a feasibility study was guided by the SPIRIT 2013 Checklist (Additional file 2).

### Eligibility

Participants will be recruited from local neighbourhoods (households) and community centres across the wide geographic area of Birmingham, UK.

#### Inclusion criteria

The following are the inclusion criteria:Community-dwelling older adults aged 60 years and older;Previously sedentary (i.e. as defined by a lack of regular involvement in more than 20 min exercise per week over the past month that increased breathing significantly and was considered moderate) [38];At risk of loneliness and having ≥ 6 out of 9 points on the three-item loneliness scale during the phone screening [39] (Additional file 3);Physically mobile as measured using the Short Physical Performance Battery (SPPB) [40] with a score ≥ 9 out of 12 [41];Healthy or having one or more common chronic diseases but ambulatory, without a cognitive disability as assessed by the Montreal Cognitive Assessment (MOCA) [42] with a score ≥ 22 out of 30 [43];Able to give written informed consent;English speaking and able to complete paper and pencil questionnaires.

#### Exclusion criteria

The following are the exclusion criteria:< 60 years old;Currently taking part in another physical activity intervention;Socially active or not lonely based on the phone screening tool by Hughes et al. [39];Regularly physically active;Moderate to severe cognitive disability with cut-off below 22 for MOCA or clinical diagnosis of dementia or Alzheimer’s disease;Not ambulatory, i.e. not able to walk 4 m;Not literate in English (speaking and reading) as this precludes taking pen and paper tests.

### Interventions

The PAIL feasibility study is a 12-week intervention consisting of group walking and health educational/social interaction workshops performed once weekly for a duration of up to 90 min per session. The design and features of the PAIL intervention are based on the features of effective interventions that were obtained from a systematic review and meta-analysis of the existing evidence conducted by Shvedko et al. [23]. Effective interventions were physical activity (PA) rather than PA interventions with social interactions, organised in group settings versus individually or one-to-one, delivered by a medical healthcare provider versus non-qualified providers and with strongest effects obtained for diseased versus healthy populations.

Group walking sessions will be run once weekly for up to 45 min each in small groups (up to eight to nine people per group) and delivered by a trained walk leader (i.e. level 3 certified personal trainer and a group exercise instructor). Prior to the first walking session, participants in the intervention group will be asked to complete the “Par-Q and You form” [44] and will receive a copy of general practitioner (GP) letter that informs their GP about their participation in the study. Participants attending the walking intervention will join the walking leader following a specified route in varied locations at every session to maintain interest in the intervention [45]. During guided walking, the instructor will be acting as a facilitator of social contact by using in-session talks and friendly discussion between participants to reduce psychosocial tension. Walking sessions will be based on the principles of gradual progression and adaptation to PA [13]. The intensity of the walks will be monitored objectively by heart rate monitors using the age-predicted heart rate maximum (HR_max_) method [46] by calculating in advance the age-predicted zones of heart rate intensity using the formula 220 minus age in years. Additionally, the intensity of walks will be monitored subjectively using the 0–10 Borg Ratings of Perceived Exertion (RPE) Scale [47] and the talk test [48]. Participants will be provided with a standardised set of instructions about the use of the 0–10 Borg RPE Scale [47, 49] and talk test [48] to enhance their understanding of these methods before the intervention [13]. Light-to-moderate intensity walking will be monitored by the ability of participants to talk back comfortably during exercises using the talk test [48] and 2–4 on the 0–10 Borg RPE scale [47]. A warm-up will be performed at the beginning of each session for 7–10 min and will include preparatory dynamic and static stretches standing, performed for the major muscle groups and walking at a leisurely pace maintaining an upright pose. At the end of the walk, participants will perform up to 10 min of balance training recommended for older adults to reduce frailty [50]. A further cool down will be performed at the end of the walking session for 5–7 min and will consist of stretching exercises for upper and lower body performed in two regimes: maintenance (e.g. maintenance of the muscle length) and developmental stretches (e.g. involving the gradual lengthening of a muscle group into an elongated position and subsequent “hold” of this position). At the end of the cool-down, participants will perform breathing exercises while standing for about 2 min.

Group walking sessions will be followed by the health education/social interactions workshops delivered in the form of a group presentation weekly for up to 45 min by the researcher (PhD student) on a variety of healthy ageing topics such as eye hygiene, mental health and well-being, preventing falls, social support, nutritional guidelines and physical activity recommendations for older adults (Additional file 4).

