#### WLC group

Participants in the wait-list control (delayed intervention) group will start the intervention after their follow-up measures are completed approximately 12 weeks post-randomisation.

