### Sample size

As this will be the feasibility study to inform the design of the future large-scale RCT, a total target sample of 40 older adult participants will be recruited for estimation of the critical parameters [63] with 20 in the intervention group and 20 in the wait-list control group.

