### Statistical methods

#### Quantitative data analysis

Quantitative data will be analysed using SPSS version 22.0 for Windows (SPSS Inc., Chicago, IL) employing an intention-to-treat analysis (based on their treatment allocation and irrespective of participants’ adherence or withdrawal) [68]. The level of significance will be set at *p* < .05; however, any hypothesis testing is preliminary and results will be interpreted with caution as this pilot study is underpowered and the analyses based on small numbers. Baseline differences between groups for continuous data (e.g. age, BMI, resting blood pressure, number of comorbidities, cognitive and physical functioning, and outcomes of questionnaires) will be analysed using one-way ANOVA. Chi-squared tests will be applied for nominal data (e.g. gender, ethnicity, marital status, living arrangements, level of education, children and employment status). For descriptive statistics, data will be presented as means (M) and standard deviations (SD). Nominal data will be presented as number (*N*) and percentage. Mixed between (group) and within (time) repeated-measures ANOVAs with post-hoc comparisons will be applied to investigate the effect of the intervention versus control on psychosocial outcomes (loneliness, social support, support networks, depression, anxiety, self-efficacy for exercise, satisfaction with level of social contacts), expected outcomes and barriers for exercise, and accelerometer data. The accelerometer data will be analysed using the ActivPAL software V7.1.18 (PAL technologies, Scotland, UK). Recorded data will be downloaded to a computer, and data for average daily amount of stepping (step counts), average time lying and sitting (h) in increments of 15 s, average time standing (h) and energy expenditure (EE, MET/h) will be analysed using mixed between (intervention group) and within (time) ANOVAs. For the Expected Outcomes and Barriers for Habitual Exercise scale [58], additional test-retest reliability will be calculated via correlation. In order to explore which outcome measures are likely to be the most important for the main trial, Pearson’s correlations will be performed between calculated change scores over time in the experimental group for all psychosocial outcomes (Lubben’s social networks, loneliness and self-efficacy for exercise) and change scores for averaged daily physical activity (time lying/sitting (h), time standing (h), time stepping (h), step counts, sit-to-stand transitions (n) and energy equivalent (METs/h)). A power calculation and sample size estimation for a future large-scale RCT will be calculated for meaningful outcomes (e.g. loneliness or social support) using the method based on the differences in means between the intervention and control group using the G-power software Version 3.1 [62].

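### The intervention arm is treated in walking groups, but the pilot ANOVA and the planned main-trial sample size assume independent participants; if outcomes correlate within groups, both overstate precision

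*Protocol article*

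**What the plan says.** The Interventions section has the weekly walks run "in small groups (up to eight to nine people per group) and delivered by a trained walk leader", with the instructor encouraging conversation between participants. Weekly workshops in the form of a group presentation follow. Wait-list participants "will start the intervention after their follow-up measures are completed approximately 12 weeks post-randomisation" (WLC group), so grouping exists in one arm only when outcomes are measured.

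The Background lists several possible mechanisms. It singles out the tripartite model of group identification, "based on the sense of identification and social attraction to group members with shared interests and goals", as the only one successfully applied to loneliness directly in a physical activity context.

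For the analysis, Quantitative data analysis states: "Mixed between (group) and within (time) repeated-measures ANOVAs with post-hoc comparisons will be applied to investigate the effect of the intervention versus control". Arm and time are the only factors. The same section says "A power calculation and sample size estimation for a future large-scale RCT will be calculated for meaningful outcomes", by a method based on the difference in means between the two arms, in G-power. Feasibility outcomes repeats that method, and Study objectives makes the power calculation a deliverable. Walking-group membership, ICC, design effect and clustering are not mentioned anywhere in the article.

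**The concern.** This is a partially nested design: randomisation is individual, one arm is then treated in groups, and the other arm is not grouped before outcome. Contact between group members is an intended ingredient, and the outcomes include loneliness, social support and social networks. It is therefore plausible that people who walk together end up more alike on these outcomes than people who do not.

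The arm-by-time ANOVA and the two-means calculation both assume independent participants. With a positive within-group correlation, the mean of the intervention arm varies more than either method allows. The more important consequence is for the main-trial sample size, which the study promises to deliver.

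**Working it through.** **The plan's own figure.** The only stated N is "a total target sample of 40 older adult participants will be recruited for estimation of the critical parameters", "with 20 in the intervention group and 20 in the wait-list control group". It agrees with itself: 20 + 20 = 40, and 10 a month × 4 months = 40. It is not derived from power, so there is no power calculation to reproduce, and no main-trial N is given.

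**Inputs from the protocol**
- Group size: at most 8 to 9. Twenty people need at least three groups (20/9 = 2.2, rounded up), so the average is 20/3 = 6.7.
- Allocation: 1:1. Only the intervention arm is grouped.
- Significance: "The level of significance will be set at *p* < .05". Sidedness is not stated.

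**Assumptions, because the protocol gives no value**
- ICC 0.01, 0.05 and 0.10.
- Two-sided test, target power 80%, standardised effects d = 0.5 and 0.3 for illustration.
- Equal total variance in the two arms.

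**Formulas**
- Intervention-arm design effect: DE = 1 + (m − 1) × ICC. The control arm has 1.
- Variance ratio of the difference: VR = (DE + 1)/2. The required N is multiplied by the same factor.
- True SE divided by assumed SE: √VR.
- Actual power of a trial sized for 80%: Φ(2.80/√VR − 1.96).

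| m | ICC | DE | VR | SE ratio | Power |
|---|---|---|---|---|---|
| 6.7 | 0.01 | 1.06 | 1.03 | 1.01 | 79% |
| 6.7 | 0.05 | 1.28 | 1.14 | 1.07 | 75% |
| 6.7 | 0.10 | 1.57 | 1.28 | 1.13 | 70% |
| 8 | 0.01 | 1.07 | 1.035 | 1.02 | 79% |
| 8 | 0.05 | 1.35 | 1.175 | 1.08 | 73% |
| 8 | 0.10 | 1.70 | 1.35 | 1.16 | 67% |

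Example for m = 8 and ICC 0.10: DE = 1 + 7 × 0.10 = 1.70; VR = (1.70 + 1)/2 = 1.35; power = Φ(2.80/1.162 − 1.96) = Φ(0.45) = 67%.

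**In participants.** The number per arm is (1 + DE) × (2.80/d)².
- d = 0.5: 63 per arm under independence. At ICC 0.05 and 0.10 this becomes 72 and 81 (m = 6.7), or 74 and 85 (m = 8).
- d = 0.3: 175 becomes 200 and 224 (m = 6.7), or 205 and 236 (m = 8).

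**Pilot type I error.** The arm-by-time test with two time points is equivalent to a t-test on change scores. It was simulated 100,000 times with 20 against 20 and walking groups of 7, 7 and 6. At a nominal 5%, rejection under no effect was 4.9% (ICC 0), 5.3% (0.01), 6.6% (0.05) and 8.5% (0.10). Here the ICC is that of the change score.

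**The case against.** **The size rests on an ICC that the document does not give.** This stands. A reader might infer that the pilot's standard errors are wrong and the main trial too small as a matter of fact. The protocol does not support that: no ICC, target power, effect size or main-trial N is printed, and at ICC 0.01 almost nothing is lost.

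**The grouping may be looser than it looks.** A reader might also assume that the same people walk and attend workshops together for 12 weeks. The Interventions section gives a maximum group size. It does not say that membership is fixed or that workshops are held per walking group. Randomisation and concealment has the walks conducted by one student researcher, and a shared leader removes one usual source of between-group differences. Groups could also be smaller, since 10 recruits a month is about 5 a month in this arm. With groups of 5, VR is 1.10 to 1.20 and power 76% to 72% at ICC 0.05 to 0.10. All this may reduce the effect but does not establish independence.

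**No pilot decision depends on it.** Correct. Progression criteria use safety, recruitment and retention, and hypothesis tests are called preliminary. That caution, however, is about low power and small numbers, not dependence, and it does not protect the main-trial calculation.

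**The methods are provisional.** Feasibility outcomes has the team review whether the methods suit the data. The review is generic and does not name clustering, and it cannot examine walking groups if membership was not recorded. Nor is this detail simply left to an unseen analysis plan: the article names both methods.

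**Other uncertainty is larger.** Also true. With 20 per arm, the SE of a standardised difference is about √(2/20) = 0.32, and moving from d = 0.5 to 0.3 raises N per arm 2.8-fold (63 to 175). But that uncertainty can fall either way, whereas ignoring a positive ICC always makes N too small.

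**Conclusion.** The point holds in conditional form. The protocol describes grouping in one arm and fixes two methods that assume independence. For any positive within-group correlation, both err towards too much precision.

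At an assumed ICC of 0.05 to 0.10, the main-trial N would need to rise by about 14% to 28% at the average group size, or 18% to 35% at 8. These figures already reflect clustering in one arm only; applying the full design effect to both arms would overstate the problem. The inflation of pilot type I error is modest and affects tests that nobody will act on alone. This is a recommendation for main-trial planning, not a defect that invalidates the feasibility study.

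**What to change.** - Record each intervention participant's walking group and any change of group.
- Do not try to estimate an ICC from about three groups.
- In Feasibility outcomes and Quantitative data analysis, replace the two-independent-means calculation with a partially nested one: multiply the intervention-arm variance by 1 + (m − 1) × ICC, with m the expected group size, and report the main-trial N for ICC 0.01 to 0.10.
- Where pilot group differences are reported with intervals, also show them with the half-width multiplied by √VR over the same range (about 1.01 to 1.13 at m = 6.7).

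The cost is one data field and some analysis wording. Randomisation, intervention and the pilot N of 40 are unchanged. The downside is a larger calculated main-trial N, by the percentages given above.
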